## Abstract

**Background:**

Oral treatment alternatives for febrile urinary tract infections are limited in the era of increasing antimicrobial resistance. We aim to evaluate if the combination of pivmecillinam and amoxicillin/clavulanic acid is non-inferior to current alternatives for step-down therapy in adult patients with febrile urinary tract infection.

**Methods:**

We plan to perform an investigator-initiated non-inferiority trial. Adult hospitalised patients treated with 1–5 days of intravenous antibiotics for acute febrile urinary tract infection caused by extended spectrum beta-lactamase (ESBL) producing Enterobacterales will be randomised 1:1 to either control (7–10 days of either oral ciprofloxacin 500 mg twice daily or oral trimethoprim–sulfamethoxazole 800 mg/160 mg twice daily or intravenous ertapenem 1 g once daily, depending on sex, drug allergy, glomerular filtration rate and susceptibility testing) or intervention (10 days of pivmecillinam 400 mg three times daily and amoxicillin/clavulanic acid 500/125 mg three times daily). The primary outcome will be clinical cure 10 days (+/− 2 days) after antibiotic treatment completion. Clinical cure is defined as being alive with absence of fever and return to non-infected baseline of urinary tract symptoms without additional antibiotic treatment or re-hospitalisation (for urinary tract infection) based on a centralised allocation-blinded structured telephone interview. We plan to recruit 330 patients to achieve 90% power based on a sample size simulation analysis using a two-group comparison, one-sided alpha of 2.5%, an absolute non-inferiority margin of 10% and expecting 93% clinical cure rate and 10% loss to follow-up. The primary endpoint will be analysed using generalised estimated equations and reported as risk difference for both intention-to-treat and per protocol populations. Patients are planned to be recruited from at least 10 centres in Sweden from 2023 to 2026.

**Discussion:**

If the combination of pivmecillinam and amoxicillin/clavulanic acid is found to be non-inferior to the control drugs there are potential benefits in terms of tolerability, frequency of interactions, outpatient treatment, side effects, nosocomial infections and drive for further antimicrobial resistance compared to existing drugs.

**Trial registration:**

NCT05224401. Registered on February 4, 2022

## Introduction

### Background and rationale {6a}

Antimicrobial resistance (AMR) is increasing. An estimated 4.95 million deaths were associated with AMR worldwide in 2019 and the total cost of health care and loss of productivity exceeds € 1.5 billion every year in the European Union [1, 2]. Extended spectrum beta-lactamase (ESBL) producing *Enterobacterales* (EPE) is of increasing concern, often colonising the gut and intestines, and causing urinary tract infections (UTI) and bloodstream infections (BSI). ESBL-producing bacteria often carry resistance to other antibiotic classes than beta-lactam antibiotics, for instance quinolones and trimethoprim-sulfamethoxazole (TMX), which are the mainstay oral treatment for febrile UTI [3]. This can result in longer treatment durations with intravenous antibiotics, either in hospitals or in outpatient clinics, which leads to greater health care costs, increased risks of nosocomial infections for patients, less patient autonomy and increased risk or acquiring further multidrug-resistant bacteria [4].

Pivmecillinam is the oral prodrug of mecillinam, a beta-lactam discovered in the 1970s with activity against *Enterobacteriaceae* [5]. There are at least three RCTs supporting the use of pivmecillinam for treatment of uncomplicated lower urinary tract infection (UTI) in women [6–8] and one in men [9]. Pivmecillinam has been used for decades in the Nordic countries [3], showing low resistance rates (<5%) [10, 11], high tolerability in general [7] and in pregnant women [12], with little adverse effects on microbiota [13] and a low drive for further resistance [14]. Treating febrile UTI (e.g., pyelonephritis) with pivmecillinam is still controversial due to a lack of evidence from RCTs but is practiced in many institutions in Sweden, Denmark and Norway [15]. A recent prospective observational study from Norway supported the use of pivmecillinam as step-down therapy for pyelonephritis with *E. coli* bacteraemia [16] while a retrospective study of pivmecillinam in EPE-causing pyelonephritis showed high rates of clinical failure [17]. We believe that these observational studies may reflect a true association, i.e. that pivmecillinam may be sufficient for non-EPE but not for EPE. Pivmecillinam has low affinity for many beta-lactamases with preserved activity in vitro [18] but pivmecillinam is sensitive to hyperproduction of beta-lactamases [19] and to the inoculum effect with several-fold increases in MIC [20]. When pivmecillinam is co-administrated with clavulanic acid (inhibiting ESBLs), the low MIC is retained, despite high inoculum, and in vitro efficacy is improved in time-kill experiments [19–23]. There may also be some synergy between pivmecillinam and ampicillin, but the data is divergent [24]. The pivmecillinam and amoxicillin/clavulanic acid (PAC) combination has been evaluated in an observational study as pre- and post-prophylaxis for transrectal ultrasound-guided biopsy of the prostate (TRUBP) and showed lower rates of bacteraemia compared to prophylactic ciprofloxacin and with significantly fewer EPE cultured [25]. Clinical trials for the use of PAC in febrile UTI are lacking however, and a search for the PAC combination in the World Health Organisation’s International Clinical Trials Registry Platform revealed no results.

We hypothesise that PAC is non-inferior to ciprofloxacin, TMX or ertapenem as step-down therapy for acute febrile UTI caused by EPE, based on the assumption that pivmecillinam is an effective treatment for febrile UTI and that the addition of clavulanic acid ensures efficacy in patients with ESBL-producing Enterobacterales.

### Objectives [7]

#### Primary objective

To evaluate if the combination PAC (intervention) is non-inferior to ciprofloxacin, TMX or ertapenem (as one composite control group) as step-down therapy in patients with acute febrile UTI caused by extended spectrum beta-lactamase (ESBL) producing Enterobacterales (EPE).

#### Secondary objectives

To compare participants’ perception of treatment tolerability on a 1–10 scale.To compare the incidence of early study drug discontinuation between groups.To compare the incidence of additional antibiotic subscriptions (for UTI) within 28 days between groups.To compare re-admission to hospital (due to UTI-related symptoms) within 28 days between groups.To compare the incidence of drug-related serious adverse events (SAE) within 28 days between groups.To compare the all-cause mortality within 28 days between groups.To compare the recurrence prevalence of EPE (phenotypically same species) in urine cultures 10 +/− 2 days after antibiotic treatment between groups (i.e. microbiological cure).To compare the prevalence of EPE or carbapenemase-producing bacteria in faecal cultures 10 +/− 2 days after antibiotic treatment between groups.

### Trial design {8}

Investigator-initiated, randomised, controlled, investigator-blinded, outcome-assessor-blinded, non-inferiority, multicentre, phase IV trial with parallel group design, 1:1 concealed allocation ratio and a 28-day follow-up period.

## Methods: participants, interventions and outcomes

### Study setting {9}

We will recruit patients from up to 29 infectious disease (ID) clinics in secondary and tertiary, emergency and teaching hospitals in Sweden. Participant recruitment 2023 in the following five Swedish ID clinics: Helsingborg, Malmö, Lund, Kristianstad and Västerås. A full list of currently recruiting centres will be updated on https://classic.clinicaltrials.gov/ct2/show/NCT05224401 and on the trial homepage: https://pacuti.se/.

### Eligibility criteria {10}

Patients will be screened for eligibility by the attending ward physician using the following criteria:

#### Inclusion criteria (all of the following)

Age ≥ 18 yearsFever (≥ 38.3 °C) or shaking chills at least once at home or in hospitalClinical suspicion of UTI including at least one of the following symptoms:aDysuria, urinary urgency, difficulty urinating, new or worsened urinary incontinence, macroscopic haematuria or increased urinary frequencybLow abdominal pain or flank pain with percussion or palpation tenderness over kidneys and/or bladder.Urine (≥ 10^3^ CFU/mL) and/or blood culture positive for EPE^1^ with susceptibility to pivmecillinam^2^.In-patient who has received 1–5 days of EPE-active^3^ intravenous antibioticsDiscontinuing parenteral treatment and starting treatment with oral antibiotics is considered safe according to the treating physician.

#### Exclusion criteria (any of the following)

Known or suspected pregnancy.Known or suspected life-threatening allergy towards beta-lactam antibiotics.Clinical isolate of EPE is resistant to ciprofloxacin, TMX and ertapenem.Severe renal insufficiency with estimated glomerular filtration rate (eGFR) <10 mL/min or requiring any form of dialysis.Severe decompensated liver failure (i.e. child Pugh class B or C).Genetic metabolic diseases associated with severe carnitine deficiency.Megaloblastic haematopoiesis.Co-treatment with valproate or valproic acid (due to interaction with pivmecillinam and ertapenem, respectively)Other reason to which patient is unfit to be included in the study according to treating physician, e.g. cognitive impairment preventing informed consent and follow-up, inability to speak and/or read Swedish, missing national personal identification number or missing telephone number preventing follow-up or planned duration of antibiotics >10 days due to complicating factors.

### Who will take informed consent? {26a}

A limited number of infectious disease physicians at each site will be responsible for obtaining informed consent from trial participants prior to treatment allocation. These physicians will receive specific training and instructions on how to follow protocol and how to collect and record data in the trial. The physicians will provide oral and written information about the study, any risks or benefits involved with participation and inform potential participants that termination from the study can be done at any time without explanation in accordance with the ethical approval. Written information will be provided after all eligibility criteria is fulfilled on days 1–5 from the initiation of EPE-active intravenous antibiotic. Recruiting physicians are asked to provide at least a few hours for each participant to contemplate their participation.

### Additional consent provisions for collection and use of participant data and biological specimens {26b}

No additional participant data or biological specimens will be collected other than what is specified in this protocol. The data collected for this study may be used in ancillary studies after approval of an amendment to the Swedish ethical review authority.

## Interventions

### Explanation for the choice of comparators {6b}

#### Drug choice

Fluoroquinolones and trimethoprim–sulfamethoxazole are considered international standard oral treatment for febrile UTI [3] and have been used since more than 20 years [28]. We use oral ciprofloxacin (500 mg twice daily) in our study based on local tradition, but oral levofloxacin (750 mg once daily) would have been an equally good choice [29]. Oral fluoroquinolones can be considered superior to oral trimethoprim–sulfamethoxazole (800 mg/160 mg twice daily) as an empirical therapy based on higher resistance rates for trimethoprim–sulfamethoxazole [30] but they are considered equally good choices when resistance patterns are known, which will be the case in our study [3]. For EPE strains with resistance to both ciprofloxacin and TMX (probably >30% of samples), the study protocol recommends intravenous ertapenem (1 g once daily). Ertapenem has been evaluated in at least 4 randomised controlled trials (RCTs) and proved equally effective and tolerable for the treatment of complicated UTI as a traditional treatment with a third-generation cephalosporin [31–33]. Ertapenem is widely used as once daily intravenous outpatient treatment of EPE-caused febrile UTIs with retrospective data supporting good clinical outcomes [34, 35] that are comparable to TMX [36].

#### Treatment duration

A 7-day course of ciprofloxacin has been shown to be non-inferior to a 14-day course in women in an RCT [37]. There is retrospective data indicating that a 7-day course may also be adequate for trimethoprim–sulfamethoxazole [38] but data from randomised trials are lacking and in practice a 10-day course in often used [39]. In men, a 2-week course of ciprofloxacin was non-inferior to a 4-week course [40]. In a more recent trial, a 7-day course of ciprofloxacin was inferior to a 14-day course of ciprofloxacin in short-time follow-up (10–18 days) but not in long-term follow-up (70–84 days post treatment) [41]. In a randomised trial of afebrile and haemodynamically stable patients with gram-negative bacteraemia where 47% were men and 68% had UTI, 7 days of antibiotics was non-inferior to 14 days [42]. In clinical practice [28] and for the purpose of our study, we consider a total treatment duration of 10 days to be reasonable for all drugs except ciprofloxacin in women where 7 days have been proved to be equally effective [37].

### Intervention description {11a}

#### Control

After 1–5 days of EPE-active intravenous antibiotics switchover to treatment^4^ totalling 10 days of either oral ciprofloxacin (500 mg twice daily^5^) or oral TMX (800 mg/160mg twice daily^6^) or intravenous ertapenem^5^ (1 g once daily^5^) for men and 7 days of ciprofloxacin (500 mg twice daily) or^6^ 10 days oral TMX (800 mg/160 mg twice daily) or^6^ intravenous ertapenem (1 g once daily) for women (Table 1 and 2).

**Table 1 Tab1:** Protocol-suggested drug in control group according to susceptibility

Susceptibility	Ciprofloxacin S	Ciprofloxacin R
TMX S	TMX^a^ (~25%)	TMX^a^ (~10%)
TMX R	Ciprofloxacin^b^ (~25%)	Ertapenem (~40%)

*S* Susceptible, *R* Resistant, according to EUCAST breakpoints [26]. Percentages refer to the *expected* (unpublished) allocation of patients between the different groups in the study, i.e. approximately total TMX 35%, Ciprofloxacin 25% and Ertapenem 40%

^a^Participants with eGFR < 20 ml/min should receive ciprofloxacin or ertapenem instead, depending on susceptibility testing and any drug allergy and/or co-treatments

^b^Participants with suspected or known aortic aneurysm, myasthenia gravis or long QT-syndrome should be treated with TMX or ertapenem depending on susceptibility testing and any drug allergy and/or co-treatments

**Table 2 Tab2:** Overview of drug interactions

**Study drug**	**Co-medication/s**	**Expected effect**
Amoxicillin/clavulanic acid	Acenocoumarol, Warfarin	Increased INR. Monitor regularly
Amoxicillin/clavulanic acid	Methotrexate	Increased concentration of co-medication
Amoxicillin/clavulanic acid	Probenecid	Increased concentration of study drug
Amoxicillin/clavulanic acid	Mycophenolic acid	Decreased concentration of co-medication
Pivmecillinam	Probenecid	Increased concentration of study drug
Pivmecillinam	Methotrexate	Increased concentration of co-medication
Pivmecillinam	Valproate/valproic acid	Both drugs decrease carnitine levels which could increase risk for hyperammonaemia
Ciprofloxacin	Class IA and III antiarrhythmics, tricyclic antidepressants, macrolides, antipsychotics	Both study drug and co-medication lead to QT-elongation
Ciprofloxacin	Probenecid, Omeprazol	Increased concentration of study drug
Ciprofloxacin	Tizanidine, Methotrexate, Duloxetine, Ropinirole, Clozapine, Sildenafil, Agomelatine, Zolpidem, Theophylline, Phenytoin, Glibenclamide	Increased concentration of co-medication. Consider therapeutic drug monitoring.
Ciprofloxacin	Cyclosporine	Increase in serum creatinine
Ciprofloxacin	Vitamin K-antagonists	Increase in anticoagulant effect. Monitor INR.
Trimetoprim–sulfamethoxazole	Dofetilid, Amantadine, Digoxin, Memantine, Metformin, Methotrexate, Lamivudine, Paclitaxel, Amiodarone, Dapsone, Repaglinide, Rosiglitazone, Pioglitazone, Coumarins, Phenytoin. Sulfonylurea derivatives	Increased serum concentration of co-medication. Consider therapeutic drug monitoring.
Trimetoprim–sulfamethoxazole	Clozapine	Risk of agranulocytosis
Trimetoprim–sulfamethoxazole	Ciclosporin, Tacrolimus	Risk of decreased kidney function in kidney transplanted patients
Trimetoprim–sulfamethoxazole	Zidovudine, Azathioprine, Mercaptopurine	Risk of haematological dysfunction
Trimetoprim–sulfamethoxazole	ACE-inhibitors, Angiotensin receptor blockers, Potassium saving diuretics, Prednisolone	Risk of hyperkalaemia
Trimetoprim–sulfamethoxazole	Thiazides	Risk of thrombocytopenia
Trimetoprim–sulfamethoxazole	Tricyclic antidepressants	Decreased concentration of co-medication
Trimetoprim–sulfamethoxazole	Pyrimethamine	Risk of anaemia
Ertapenem	Valproate/Valproic acid	Decreased concentration of co-medication

#### Intervention

After 1–5 days of EPE-active intravenous antibiotics switch-over to treatment totalling 10 days of oral pivmecillinam (400 mg three times daily^5^) and oral amoxicillin/clavulanic acid (500/125 mg three times daily^5^) for both men and women.

### Criteria for discontinuing or modifying allocated interventions {11b}

There are no mandated criteria for discontinuing or modifying allocated interventions, but the patient and the treating physician may choose to do so at any time, upon which they will be asked to report timing and reason for non-adherence.

### Strategies to improve adherence to interventions {11c}

Intervention adherence while in hospital will be monitored by the treating physician and any deviance will be required to be registered in the electronic case report form (eCRF). After patients are dismissed, the allocation-blinded outcome-assessor (the research nurse) will ask the participant whether he or she has taken all the medicines as prescribed, if not why, and how the participant perceived the treatment tolerability, and if any he or she have received any further antibiotic prescriptions for UTI since recruitment to the trial. Even though this pragmatic monitoring cannot guarantee adherence with certainty, it is similar to the how the medications would be used in the clinic. The recruiting physician will further validate that the participants have collected their study drug prescription, and that they have not received any further prescriptions, during the retrospective medical journal review.

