### Outcomes [12]

#### Primary outcome

Clinical cure 10 days (+/− 2 days, i.e. weekends) after antibiotic treatment completion defined as being alive with absence of fever (≥ 38.3 °C) and resolution of, or return to non-infected baseline of, urinary tract symptoms (as defined in inclusion criteria) without hospital readmission (for UTI symptoms) or additional antibiotic treatment (for UTI symptoms) based on a structured telephone interview performed by a centralised allocation-blinded study nurse.

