## Assignment of interventions: blinding

### Who will be blinded {17a}

Trial participants and in-patient care providers will not be blinded to interventions in this pragmatic trial. Neither will the treating physician who assesses secondary endpoints 2-8. However, the central outcome assessor of the primary outcome will be blinded to interventions, as will the trial investigators, data analysts and author group. When data is extracted from the REDCap database, the allocation will be coded as “1” and “2” and the Code Key will only be revealed after statistical evaluation of the primary and secondary endpoints.

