## Data collection and management

### Plans for assessment and collection of outcomes {18a}

Baseline data and allocation will be entered into the REDCap database using a short and study-specific electronic case report form (eCRF) directly when assessing eligibility and assigning allocation by the physician who recruited the participant. The trial investigators will instruct a limited number of physicians at participating centre how to access and fill out the eCRF and provide a step-by-step guide and contact information for technical assistance. The primary outcome and the secondary outcomes 2-4 will be assessed using a semi-structured interview with a trial-specific guideline and entered into a separate part of the REDCap eCRF. The first 10 participants’ interview responses will be checked for conformity between at least two study nurses. The remaining secondary outcomes will be assessed retrospectively through medical chart review and from microbiological results by the recruiting physician at 30–60 days after the patient was allocated and then entered into a final separate part of the eCRF. The retrospective chart review will also serve as a sensitivity analysis to the telephone interview for the primary outcome and the secondary outcomes of early drug discontinuation and further antibiotic prescription. A copy of the REDCap eCRF (English) and semi-structured interview guideline (Swedish) can be sent on request.

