## Discussion

### Methodology

Choosing a non-inferiority design always constitutes a compromise in scientific validity compared to a placebo-controlled superiority trial. However, giving patients with serious infections placebo is not ethical, and because EPE-causing febrile UTI is (yet) uncommon in Sweden, we considered a non-inferiority trial to be the best compromise. This enables a high possibility for completing the trial with our available resources and within a reasonable timeframe. The implementation of a surveillance system for EPE in urine and blood cultures in Swedish microbiology departments should be an effective method to ensure consistent recruitment.

Preferably, the treating and recruiting physician and other healthcare personnel would be blinded to treatment allocation. With our design, using three oral and one intravenous antimicrobial, with one to three doses daily, it was overwhelming to us, both in complexity and cost, to design a completely blinded intervention. This non-blinding may affect how patients are treated and how the protocol is adhered. Part of this bias may be managed by analysing the primary outcome both as ITT, mITT and PP. We have put efforts into keeping the primary outcome assessor blinded and stringent in their assessment through the use of a few trained centralised assessors using a study-specific structured interview.

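### The allocation-blinded nurse who scores clinical cure also asks unblinded participants about their medicines; this is likely to unblind the assessor for some participants, and the article describes no safeguard

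*Protocol article*

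**What the plan says.** - **Who is blinded.** Section {17a} states that "Trial participants and in-patient care providers will not be blinded to interventions in this pragmatic trial", while "the central outcome assessor of the primary outcome will be blinded to interventions".
- **How cure is scored.** Under Primary outcome, cure requires survival, no fever, urinary symptoms gone or back to the participant's usual level, and no readmission or further antibiotics for urinary infection, "based on a structured telephone interview performed by a centralised allocation-blinded study nurse".
- **What else the nurse asks.** Section {11c} says that, after discharge, "the allocation-blinded outcome-assessor (the research nurse) will ask the participant whether he or she has taken all the medicines as prescribed, if not why". The list continues with "how the participant perceived the treatment tolerability" and with any new antibiotics for urinary infection.
- **What the interview collects.** Section {18a} says: "The primary outcome and the secondary outcomes 2-4 will be assessed using a semi-structured interview with a trial-specific guideline". Secondary outcome 2 is early discontinuation of the study drug, so a question about stopping treatment belongs to the same interview as the cure items.
- **What rests on the blind.** The Methodology part of the Discussion concedes that full blinding was not feasible and then says: "We have put efforts into keeping the primary outcome assessor blinded and stringent in their assessment". The Discussion also describes clinical cure as a mainly subjective outcome.

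Section {18a} mentions an interview guideline and the eCRF, both available on request. Neither is part of the article.

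**The concern.** One person is asked both to stay unaware of the arm and to discuss study medicines with people who know it. The regimens differ in ways that come up easily in conversation: two oral drugs three times daily (PAC), one oral drug twice daily (ciprofloxacin or trimethoprim-sulfamethoxazole), or a once-daily infusion (ertapenem, expected in about 40% of controls by Table 1).

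The part of cure most open to judgement is whether residual urinary symptoms have returned to the participant's usual level. If the nurse knows the arm when deciding this, scoring can drift towards expectation in either direction. Drift in favour of PAC raises the chance of a false claim of non-inferiority; drift against PAC costs power. The margin is 10 points and expected cure is 93%, so few failures are expected and a handful of rescored participants matters.

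**Working it through.** **1. Can the questions disclose the arm?**

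- The adherence question can be answered with a plain yes, and tolerability is a score from 1 to 10. No section has the nurse ask for the drug's name, route or number of tablets.
- A participant who did not take everything is asked why. The answer can easily mention the drug, the number of drugs or an infusion.
- Section {20c} allows at most two missed doses for the per-protocol set. After discharge, the nurse's question is the only source that the article describes on doses taken; the recruiting physician confirms only that the prescription was collected ({11c}). Missed doses therefore have to be probed.
- Disclosure is thus likely for some participants, and most likely for those who stopped early. Section {18b} itself expects many who deviate to be scored as negative outcomes.

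**2. Do the described checks protect the scoring?**

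- Discordance between telephone and chart counts as failure ({20a}, Table 3 footnote). This catches readmissions and prescriptions that the call missed. It is unlikely to catch residual symptoms mentioned only by telephone, and it never turns a failure scored by the nurse back into a cure.
- The chart review is done by the recruiting or treating physician ({18a}, {19}), who is not blinded ({17a}).
- Coding the arms as 1 and 2 protects the analysts, not the interviewer. Running ITT, mITT and per-protocol analyses does not correct biased scoring.

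**3. The plan's own figure.** Inputs from Sample size {14}: cure 93% (taken for both arms), margin 10 points, one-sided alpha 2.5%, 300 evaluable participants, hence 150 per arm at 1:1.

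SE = √(2 × 0.93 × 0.07 / 150) = 0.0295. Power = Φ(0.10/0.0295 − 1.96) = Φ(1.43) = 92.4%.

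Simulating 30 sites of 10 with intraclass correlation 0.1 gives 91.2% with simple allocation within site, and 92.7 to 93.5% with balanced sites. The stated 90% is reproduced to within about 2 points by the first variant and is mildly conservative under the others. The simple formula is adequate for the illustration below.

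**4. Illustration of biased scoring.** The rates of biased scoring are assumptions; the documents give none. With p₁ the scored cure rate on PAC and p₀ that on control,

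P(non-inferiority declared) = Φ((p₁ − p₀ + 0.10)/SE − 1.96), SE = √([p₁(1 − p₁) + p₀(1 − p₀)]/150).

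*True difference −10 points (PAC 83%, control 93%).* The result is the one-sided error. Scored PAC cure is 0.83 + 0.17q.

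| PAC failures scored as cures (q) | Scored PAC cure | Error |
|---|---|---|
| 0% | 83.0% | 2.5% |
| 5% | 83.85% | 4.2% |
| 10% | 84.7% | 6.8% |
| 20% | 86.4% | 16.2% |

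*Equal true cure of 93%.* The result is power. Scored PAC cure is 0.93(1 − q).

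| PAC cures scored as failures (q) | Scored PAC cure | Power |
|---|---|---|
| 0% | 93.0% | 92.4% |
| 1% | 92.07% | 84.8% |
| 2% | 91.14% | 74.2% |
| 3% | 90.21% | 61.6% |

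In participants: 17% of 150 is 25.5 PAC failures, so 5 to 20% is about 1 to 5 people. Likewise 93% of 150 is 139.5 PAC cures, so 1 to 3% is about 1 to 4 people.

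**The case against.** The strongest reply is that the article condenses a fuller protocol. Question order, form locking and the rule that derives cure normally sit in the interview guide and eCRF, which exist but are not shown. The guide may already protect the blind. This stands, and it means that a failure of blinding cannot be asserted.

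Some checks also count in the plan's favour: a few trained central assessors, comparison of the first 10 participants' responses between at least two nurses, the discordance rule, and a sensitivity analysis on chart review. They narrow the exposure but leave residual symptoms reported only by telephone largely uncovered.

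A reader might infer that these questions reveal the arm outright and undo the blinding, or that about 70% of participants are identifiable (all of PAC plus 40% of controls: 0.5 × 1 + 0.5 × 0.40 = 0.70). The documents do not support this. The 70% assumes that every such participant describes the regimen, so it is an upper bound and not an estimate. Every participant also had 1 to 5 days of intravenous antibiotics before the switch, so mention of an infusion does not by itself point to ertapenem. Nor do tolerability complaints reliably identify the arm when the control group mixes three drugs.

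Finally, unblinded participants report their own symptoms. That bias comes with open-label treatment, and no ordering of questions removes it.

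**Conclusion.** The point holds as a likely and avoidable risk, not as a demonstrated loss of blinding. The text gives blinded scoring of a largely subjective outcome and questions about study medicines to the same nurse, and relies on that blind to defend an open-label design. Unblinding is likely for some participants, particularly those who stopped early or had intravenous ertapenem, and the article describes no safeguard.

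The size is unknown. The illustrated ranges (one-sided error about 4 to 16%, or power about 85 to 62%) rest on assumed rates of biased scoring, bias in one arm only, 150 per arm and no allowance for clustering. They show that a few rescored participants matter against this margin; they do not predict what will happen.

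Separately, the interview is called structured in the Abstract, under Primary outcome and in the Discussion, but semi-structured in {18a}. The two terms imply different room for the nurse's judgement and need to be reconciled.

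**What to change.** In the interview guide and eCRF:

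1. Open with a scripted request not to mention the study treatment.
2. Ask the cure items first, as closed questions: fever, each urinary symptom compared with the state before the infection, readmission for urinary infection, and new antibiotics for it.
3. Derive cure or failure by a database rule and lock that form.
4. Only then open the questions on adherence, discontinuation and tolerability.
5. Record whether the arm became known before the lock, and report this by arm.

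Use one term for the interview throughout. If the guide already works this way, a sentence in {17a} or {18a} saying so settles the point.

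The cost is a re-ordered guide and a form lock in REDCap, with the same nurse, the same call and no added staff. Recruitment began in April 2023, so the date of any change should be logged to tell earlier interviews from later ones.
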